### Evaluation of safety

2.10

The frequency of adverse events will be the main focus of the safety assessment. Any negative experiences, such as pain, bleeding, bruises, infection, and dizziness, will be reported by participants. At every evaluation, the researcher will record and assess all adverse occurrences on a standardized adverse event form, regardless of whether they are thought to be connected to the acupuncture therapy. Records will be kept of the onset time, duration, severity (mild, moderate, or severe), management strategy, resolution time, and causation assessment (definite, probable, improbable, or irrelevant).

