In addition, although the following measures will not reduce the placebo effect, we will take further steps to ensure the overall scientific rigor and interpretability of the study results. Baseline characteristics of all participants will be compared to verify the comparability between the tinnitus and healthy control groups. During recruitment, participants will be provided with standardized information regarding the study procedures, potential benefits, possible adverse reactions, and the sensory experiences associated with acupuncture. The information will be presented in a balanced manner to ensure adequate understanding of the intervention without emphasizing potential treatment outcomes. Furthermore, subjective questionnaire data will be evaluated alongside objective ABR measures to provide complementary information regarding clinical changes and associated neurophysiological alterations. The Standard Protocol Items: Recommendations for Interventional Trials (SPIRIT) guidelines will be followed in the development of the protocol (29). Zhejiang Chinese Medical University’s Third Affiliated Hospital will host the study. A total of 72 participants will be included in this study, including 36 patients with chronic tinnitus and 36 healthy controls who matched the patient in age and sex. Healthy controls will be individually matched with tinnitus participants according to sex and age within ±3 years. In addition to demographic matching, we will also compare PTA and audiogram characteristics between the two groups at baseline, as well as before and after treatment within each group. If there are significant intergroup differences in audiogram characteristics, these specific frequencies will be included as covariates in the statistical model used to compare auditory brainstem response (ABR) parameters between groups. The treatment plan includes 10 sessions of acupuncture, which can be completed within 4 weeks and carried out three times a week (usually 2 days apart between each treatment). There are three time points used to evaluate tinnitus-related clinical outcomes and auditory brainstem response (ABR) parameters, namely the baseline period (before the start of treatment), the end of the course (within 1 week after the tenth treatment), and the 8th week after the completion of treatment as follow-up point. The Institutional Ethical Review Board (IRB) of the Third Affiliated Hospital of Zhejiang Chinese Medical University has granted ethical permission for the trial (ZSLL-KY-2025-032-01), which will be conducted in accordance with the Declaration of Helsinki. The Ethics Committee will be notified right away of any amendments to the study design. NCT07522567 is the identification code for this trial’s registration in the Clinical Trials Registry. Table 1 displays the study’s SPIRIT list, while Figure 1 displays the flow diagram.

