
**Table 1 tab1:** SPIRIT schedule of enrollment, interventions, and assessments.

	Study period							
	Enrolment	Allocation	Treatment period				Post-treatment	Follow-up
TIMEPOINT (week)	Week −1(T0)	Week 0	W1	W2	W3	W4	W5 (T1)	W13 (T2: 8-week FU)
Enrolment								
Eligibility screen	X							
Informed consent	X							
Demographic/medical history	X							
Allocation		X						
Interventions								
Acupuncture (10 sessions, 3×/week)			X	X	X	X		
Assessments								
ABR parameters	X						X	
Pure-Tone Threshold testing	X							
Tympanometry & Acoustic reflex testing	X							
DPOAEs	X							
Otoscopic examination	X							
THI	X						X	X
TEQ	X						X	X
Loudness/Annoyance VAS	X						X	X
Adverse events			X	X	X	X	X	

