### Outcome measures

2.7

The outcomes of this study were designed to evaluate both the clinical efficacy and neurophysiological changes associated with acupuncture treatment in patients with chronic tinnitus. Considering the different characteristics of subjective symptom assessment and electrophysiological evaluation, clinical and neurophysiological outcomes will be analyzed separately.

The assessment schedule is summarized in Table 1. Patient-reported outcomes, including tinnitus severity and related functional impairment, will be assessed at baseline (T0), after completion of acupuncture treatment (T1), and at the 8-week (after the beginning of acupuncture treatment) follow-up visit (T2). Auditory brainstem response (ABR) measurements will be performed in both the healthy control group and the tinnitus patient group at baseline (T0) and after treatment completion (T1), as the primary purpose of the electrophysiological assessment is to evaluate changes in auditory pathway function during the course of treatment. ABR testing will not be conducted at the follow-up visit, as the primary purpose of the follow-up assessment is to evaluate the durability of subjective tinnitus improvement.

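### Section 2.10 has adverse events recorded at every evaluation, but the adverse-event row of Table 1 is blank at the follow-up evaluation T2

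*Protocol article*

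**What the plan says.** Section 2.10 (Evaluation of safety) makes the frequency of adverse events the chief safety measure. Its collection rule is: "At every evaluation, the researcher will record and assess all adverse occurrences on a standardized adverse event form". The rule covers all events, whether or not acupuncture is thought to be the cause. The items are listed as follows: "Records will be kept of the onset time, duration, severity (mild, moderate, or severe), management strategy, resolution time, and causation assessment".

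Table 1 (SPIRIT schedule, section 2.1) has eight time columns: week −1 (T0), week 0, W1, W2, W3, W4, W5 (T1) and W13 (T2). The row labelled "Adverse events" is marked in W1 to W4 and in W5. The W13 cell is empty.

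T2 is treated as an evaluation throughout. Section 2.1 says "There are three time points used to evaluate tinnitus-related clinical outcomes and auditory brainstem response (ABR) parameters" and names the follow-up as the third. Section 2.7 schedules the patient-reported outcomes at T2 and refers the reader to Table 1 for the assessment schedule. Section 3.1 describes the follow-up as an assessment made by telephone.

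**The concern.** Read literally, the rule in section 2.10 includes T2, while the schedule leaves it out. Nothing in the article exempts T2 from adverse-event recording. Since section 2.7 points to Table 1 for the schedule, staff could reasonably take the table as their working instruction.

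The observation window of the main safety measure is at stake. A count of events up to T1 and a count up to T2 are different quantities, and the article supports both. The required items on duration and resolution are also affected. T1 falls within one week of the tenth session, so an event arising from the last sessions may still be open when it is last asked about.

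**Working it through.** No formula or sample-size input is involved. The check sets the rule beside the schedule and measures the gap.

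**1. Position of the marks in Table 1.** The cells of each row were counted against the eight column headings.

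| Row | Columns marked |
|---|---|
| Acupuncture | 3–6 (W1–W4) |
| THI, TEQ, VAS | 1, 7, 8 (T0, T1, T2) |
| Adverse events | 3–7 (W1–W4, T1) |

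The acupuncture and questionnaire rows fall where the text says they should, so the columns are aligned. The blank under T2 in the adverse-event row is therefore unlikely to be a fault of text extraction. Five of eight columns are marked.

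**2. Rule against schedule at the three evaluations.**

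| Evaluation | Section 2.10 | Table 1 |
|---|---|---|
| T0 | included by the wording | blank |
| T1 | included | marked |
| T2 | included by the wording | blank |

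T0 precedes treatment, so its blank cell matters little. T2 is the only evaluation after treatment starts at which the two places disagree.

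**3. Length of the unscheduled stretch.** This depends on when T2 takes place, and the article is not consistent about that.

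- Table 1 labels: W13 − W5 = 8 weeks.
- Section 2.1 (T2 in the eighth week after treatment ends, T1 within one week of the last session): 8 − 1 = 7 to 8 − 0 = 8 weeks.
- Section 2.7 (T2 eight weeks after treatment begins): if the start is taken as week 0, T2 is at week 8 and the gap is 8 − 5 = 3 weeks. If it is taken as week 1, T2 is at week 9 and the gap is 9 − 5 = 4 weeks.

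The gap is thus about 8 weeks on two of the descriptions and about 3 to 4 weeks on the third. It does not vanish on any of them.

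**4. What follows if the table is used.** No contact after T1 is scheduled to ask about adverse events. An event open at T1 has no planned occasion for recording its end, and an event that begins later is recorded only if the participant volunteers it.

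**The case against.** The strongest reply is that the phrase about every evaluation stands under a heading on safety and may mean every scheduled safety evaluation. Table 1 gives this some support. Adverse events are marked in W1 to W4, where no outcome is assessed, and not at T0, where all outcomes are. Section 2.7 says the follow-up is there to show whether symptom improvement lasts. Ending collection at T1 could be deliberate. That reading is possible, but the article does not state it, and section 2.10 refers to evaluations without qualification. The ambiguity remains and needs a decision.

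A reader might go further and infer that the follow-up gathers no safety data at all, or that resolution times cannot be completed. The document does not support either. The first holds only if Table 1 overrides section 2.10; if section 2.10 governs, T2 is covered and the table merely lacks a mark. As to the second, section 2.10 relies on participants to report events, and nothing forbids updating an open record outside a marked cell. Nor should a fixed 8-week loss be claimed, given the conflicting timing of T2. Because this is a single-centre study, there is also no question of several sites reading the schedule differently.

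The point about size stands: the events named in section 2.10 are mostly short-lived, and the treatment weeks and T1 are covered.

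**Conclusion.** The inconsistency is real. The text requires adverse events at every evaluation, with resolution time, and the schedule omits them at T2. If staff follow the table, adverse events are not scheduled to be asked about after T1, for about 8 weeks by Table 1 or about 3 to 4 weeks on the timing in section 2.7. Events open at T1 then lack a planned contact for recording resolution, and later events may be missed.

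This is a minor point. The article gives no event rate, so the number of events affected cannot be calculated; the judgement that it is small rests on the kind of events listed and on the coverage up to T1. No efficacy endpoint, error rate or sample size is affected. The conclusion assumes that T2 counts as an evaluation in the sense of section 2.10, which sections 2.1, 2.7 and 3.1 support.

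**What to change.** Reconcile section 2.10 and Table 1 by marking adverse events in the T2 column. At the existing telephone contact, ask two things: whether events still open at T1 have resolved and when, and whether any new events have occurred since. State in section 2.10 that the adverse-event frequency covers the period up to T2, and align the timing of T2 across sections 2.1 and 2.7 and Table 1 so that this period has a defined length.

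The cost is one mark in the table, a sentence or two of text, and a few more questions in a call that already takes place. Answers given by telephone carry the recall problem that section 3.1 already acknowledges for the questionnaires.

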## Discussion

3

This study protocol is a two-phase clinical inquiry intended to assess the neurophysiological effects of acupuncture and investigate the connection between auditory brainstem function and chronic tinnitus. To our knowledge, this is one of the first studies to integrate ABR measurements with a standardized acupuncture intervention within a matched case–control and self-controlled design. This study is expected to provide insights into both the pathophysiological mechanisms of chronic tinnitus and the neurophysiological effects of acupuncture.

The first part of this study will compare the ABR parameters between patients and the healthy participants with age and sex matching. With the accumulation of existing evidence, we put forward a hypothesis that patients with chronic tinnitus will have specific ABR abnormalities, especially the amplitude reduction of wave I and (or) the prolongation of the latency of wave V. This hypothesis is based on the currently accepted model of cochlear synapsis, which refers to the selective loss of synapses between the internal hair cells and the auditory nerve. Even if the hearing threshold is normal, this kind of synaptic loss may occur (41). This condition, in which cochlear synapse loss occurs without affecting pure-tone thresholds, has been termed ‘hidden hearing loss’ (HHL) (22). In animal models, noise exposure can cause permanent loss of cochlear nerve synapses, with a loss rate of up to 50%. Although the cochlea threshold has been fully recovered at this time, the ABR wave I amplitude can still be used as a reliable non-invasive correlation indicator of synaptic density (42, 43). It has always been challenging to extrapolate these animal research findings to humans, but there are more and more successful cases. Bramhall et al. (2019) provided a comprehensive review of the methodological challenges and research progress faced in finding cochlear synaptic lesions caused by noise in humans. The conclusion of the review is that although the ABR wave I amplitude is still the most promising non-invasive biomarker, its application is limited by several factors, including height differences between subjects, individual differences in skull thickness, and limited dynamic range of the surface electrode itself (44). In order to overcome these limitations, many research teams have developed advanced signal processing technologies. Möhrle et al. (2019) adopted a new ABR experimental paradigm, which evaluates the defects in time processing through different click rates. Their research results showed that mice with evidence of behavioral tinnitus showed enhanced central nerve gain. This gain is considered to be a compensation mechanism for the loss of peripheral input. Through high-frequency stimulation, the above-mentioned neural gain can be observed (45).

The relationship between ABR abnormality and tinnitus perception will become more complicated due to individual differences in the central gain mechanism. Hofmeier et al. (46) conducted a large-scale study to find functional biomarkers that can distinguish between patients with and without hyperacusis. They found that patients with tinnitus without hyperacusis showed a prolonged latency and reduced amplitude of V waves in ABR. In contrast, patients with hearing sensitivity showed increased amplitude of III waves and V waves under high-intensity stimulation. This shows that the same peripheral damage may lead to differences in central compensation patterns due to different individual neurobiological factors. In the study of auditory brainstem response (ABR), methodological considerations are very important. A comprehensive systematic evaluation of the ABR scheme in tinnitus research by Milloy et al. (20) emphasized the importance of controlling participant characteristics, stimulation parameters, electrode placement and data analysis techniques, and pointed out that the significant heterogeneity between studies led to inconsistency in the results in the literature. In order to solve the above problems, this study adopts standardized click stimulation and tests under multiple stimulation intensities. In-ear headphones are used to optimize the attenuation effect of both ears. In addition, the study also implemented a strict quality control procedure: two independent audiologists who did not know about the group allocation interpreted the repeated recorded waveforms, respectively.

The second part of this study will evaluate the changes in ABR parameters after completing 10 acupuncture courses. In East Asia, acupuncture is widely used to treat tinnitus. Nevertheless, there is no sufficient evidence to decide whether to recommend acupuncture for the management of tinnitus. It shows that there is still an urgent need for rigorous clinical trials in this field (47). The quality of existing evidence is limited by several factors, including the small sample size, the lack of sham acupuncture controls, and the heterogeneity of the result measurement methods. These shortcomings are the goals that this study focuses on when designing. At the same time, emerging preclinical evidence shows that acupuncture may have a regulating effect on auditory function at multiple levels of the auditory pathway (48, 49). While these animal studies provide valuable mechanistic insights, their direct translation to the clinical setting requires careful consideration. Several factors limit the generalizability of these findings to our human protocol. First, animal models of tinnitus often use acute or trauma-induced conditions, whereas chronic tinnitus in humans typically evolves over years with complex peripheral and central interactions. Second, the electrophysiological end points differ: animal studies often measure ABR threshold shifts as indicators of hearing recovery, whereas our study focuses on supra-threshold latency and amplitude parameters as indicators of neural conduction and central gain. Despite these differences, the animal evidence supports the plausibility that acupuncture can modulate auditory brainstem activity, thereby providing a neurobiological rationale for our investigation. The present study will test whether these preclinical observations translate to measurable electrophysiological changes in human tinnitus patients. If the hypothesis of this study is confirmed, the findings would carry significant clinical and mechanistic implications. Demonstrating characteristic ABR profiles in chronic tinnitus patients would support the practical application of ABR as an objective biomarker for tinnitus subtyping, addressing a long-standing need for quantitative diagnostic tools in tinnitus research. Moreover, observing treatment-related changes in ABR parameters that correlate with clinical symptom improvement would provide neurophysiological evidence for acupuncture’s therapeutic effects, evidence that could extend beyond the current reliance on patient self-report and strengthen the rationale for future large-scale sham-controlled trials. The VA/DOD guidelines released in 2024 specifically put forward the following suggestions: verified subjective outcome measurement tools (such as tinnitus function index and tinnitus disorder list) should be used to monitor the treatment effect; at the same time, it is not recommended to use psychoacoustic measurement methods to achieve this purpose (47). However, the guide does not deal with electrophysiological measurement indicators such as auditory brainstem response (ABR). This omission highlights an important research gap, and this study may help fill this gap. Moreover, if treatment-related ABR parameter changes are observed, and these changes correspond to the improvement of clinical symptoms, then this will provide neurophysiological evidences for the therapeutic effect of acupuncture. These evidences can go beyond the current limitation of relying only on the subjective report of patients. This idea also coincides with the recent call for the use of objective outcome indicators in tinnitus clinical trials (50).

### Limitations and future directions

3.1

This study has a number of limitations. Its sample size is comparatively modest because it is a single-center study. Therefore, the results may not be fully extended to a wider range of people with tinnitus. Another limitation is that the intervention group did not include a tinnitus control group receiving sham treatment, making it impossible to compare the effects of true acupuncture and sham acupuncture on patients with tinnitus. This is particularly worthy of attention, because the 2024 VA/DOD guidelines found insufficient evidence of acupuncture, and thus emphasized the need to carry out good controlled trials. While the self-controlled design allows each patient to serve as their own control and reduces between-subject variability, it cannot fully distinguish specific acupuncture effects from placebo effects, regression to the mean, or non-specific treatment effects. Although the inclusion of a healthy control group with repeated ABR measurements helps quantify normal test–retest variability, it does not replace a parallel sham-controlled arm. Therefore, our findings should be interpreted as preliminary and hypothesis-generating. Future adequately powered, sham-controlled randomized trials are needed to definitively establish the efficacy of acupuncture for chronic tinnitus. Third, the ABR protocol in this study uses broadband click stimuli rather than frequency-specific tone bursts. While this choice ensures clinical standardization and comparability with previous literature, it may reduce the sensitivity to detect frequency-specific cochlear synaptopathic changes that have been suggested to underlie some forms of tinnitus (51). Future studies incorporating multiple frequency-specific stimuli (e.g., 1, 2, and 4 kHz tone bursts) would provide a more comprehensive assessment of the relationship between acupuncture, ABR parameters, and tinnitus pathophysiology. Fourth, this study employs an assessor-blinded design rather than a double-blind design. Due to the nature of the acupuncture intervention, neither patients nor acupuncturists can be blinded to treatment allocation, which may introduce performance bias and expectation effects. To mitigate this, we have implemented several measures which have been motioned in the Design overview section. Nonetheless, we acknowledge that the lack of patient blinding remains a limitation. Fifth, treatment adherence is currently assessed primarily by session attendance, which does not fully capture treatment fidelity. To strengthen this aspect, all acupuncturists will follow a detailed Standard Operating Procedure (SOP) manual, needle manipulation parameters (angle, frequency, and duration) will be recorded for each session, and the De Qi sensation will be assessed using the C-MASS scale after each session. These additional measures will allow us to characterize the consistency of treatment delivery beyond simple attendance records. In addition, although ABR measurement is valuable for evaluating brainstem function, it cannot capture changes in the cortical level, which may also affect the perception of tinnitus. Lastly, this study did not set up a long-term follow-up beyond the treatment period, so it is impossible to evaluate whether the observed effect is persistent. And the 8-week follow-up assessment was conducted by telephone, which may introduce recall bias and reduce the accuracy of symptom evaluation compared with face-to-face assessment.

In order to overcome the above limitations, future research should adopt a multi-center experimental design, incorporate a larger sample size, set up a sham acupuncture control group, and extend the follow-up observation period. In addition, the inclusion of multimodal neuroimaging evaluation (such as resting functional MRI) in the research design will help to examine the mechanism of the brainstem and cortex at the same time. This practice may build a bridge between ABR’s research findings and network-level models. Furthermore, tinnitus can be classified into various subgroups based on clinical and electrophysiological traits. Therefore, future studies should consider adopting a larger sample size so that subgroup analysis can be carried out. The integration of genetics, psychology and neuroimaging measurement methods may eventually promote personalized treatment for this heterogeneous disease. This direction is also in line with the idea put forward by the recent theoretical frameworks (52).
